### Settings

Since the CKD patients served by KPSC receive care in 13 KPSC centers spanning over 2000 mile^2^ ranging across Los Angeles and San Diego metropolitan areas, an intervention strategy and setting that can reach all of these patients needs to be employed. Also, the intervention needs to reach racial and ethnic minority patients, who often have fewer transportation resources available to them and may be less able to travel even locally to take advantage of CKD education programs. Finally, the DDKT and LDKT education program needs to be flexible and capable of integration into the ongoing transplant education and care management programs within KPSC so it does not create additional burden on busy transplant coordinators and patient educators. Thus, the setting for this *Explore Transplant@Home* trial will be guided learning within the patient’s homes, for patients and any interested individuals in their social support networks, through use of video, print, and text education.

### Intervention (RCT educational components)

#### Description of standard KPSC transplant education (control)

All KPSC nephrology departments currently offer a 1–2 h course in transplant education to all CKD patients interested in pursuing transplant, whether from a living or deceased donor. The KPSC course addresses topics including how kidney transplantation works, determining whether kidney transplantation is the right choice, the steps involved in pre-transplant evaluation and referral to transplant centers of excellence. Because time is limited, the bulk of the content covered is oriented toward developing an understanding of the evaluation and wait-listing process, rather than on the risks and benefits of pursuing LDKT. Patients are encouraged to bring any prospective donors to the class with them, and course attendees learn about the basics of donor testing, some simple information regarding matching and donor exchanges, and reminders that LDKT can result in a much shorter wait for a donor organ. Written materials and presentations from the educators do recommend that patients seek out living donors but do not provide details on how to approach prospective donors. The materials address only the risks and benefits to the recipient not to the donors. Compared to DDKT, much less detailed information is provided regarding LDKT, unless prompted by interested patients. Practical information about waiting for a transplant, including local wait-list times and allocation criteria, the transplant procedure, and steps for post-graft follow-up are covered in detail. KPSC educators include nephrology nurses and social workers. The course is presented monthly in English with available real-time language interpreters at each of 13 local medical centers, in Spanish at 1–2 centers, and is supplemented by a written pamphlet in English and Spanish.

While patients at all phases of CKD and their family members and support persons are welcome to attend the transplant education course, it is primarily focused on individuals who have reached an advanced stage of CKD and/or ESRD and are contemplating renal replacement options, or who are new to dialysis and considering transplant as a renal replacement approach. Patients who wish to be evaluated for transplant eligibility and move forward with the process of pre-transplant assessment and listing are required to complete this course before beginning pre-transplant work-up. For this trial, routine transplant education practices will be continued without any content changes. Patients who are randomized to the control condition and who are or become potentially eligible for transplant will not receive any additional interventions within KPSC during the study period.

#### Description of patient-guided *Explore Transplant@Home* program

Patients in the *ET@Home* study condition will receive four modules of video and print transplant education over a 6-month period (Table 1). The modules sequentially help patients think through what is important to them, learn what it might be like if they became a kidney recipient or involved a living donor, the risks and benefits of each, and, at the program’s conclusion, make a decision about the best treatment option for them. The four videos and their corresponding print brochures – “Exploring Transplant”, “Kidney Recipients’ Transplant Experiences,” “Living Donors’ Donation Experiences,” and “Making an Informed Choice” – discuss in detail the medical, psychological, and financial risks of being a deceased or living donor. These modules cover ways to slow down kidney disease and include real life quotes and stories from people who have stayed on dialysis, received DDKT and LDKT, or been a living donor. The “Making an Informed Choice” brochure is a decision aid that guides patients in choosing a path that is right for them and provides helpful websites that patients can use as resources to learn more. At the conclusion of the program, patients individually choose which renal replacement treatments may be right for them and plan a set of small steps they want to take next.

**Table 1 Tab1:** *Explore Transplant@Home* Module Content

Module 1: The Basics of Kidney Disease*	General Contents	Brochure	Postcards	Video
	Welcome & Info Card Video #1 (DVD or link)	“Basics of Kidney Disease” o What are kidneys and what do they do? o What is kidney disease? o What are the treatment options for kidney disease? o Why kidney patients get transplant o Why people donate their kidneys	“What is Chronic Kidney Disease?” “How can I slow down kidney disease?” “What are the treatment options for kidney failure?”	“Exploring possible treatment options” This introductory video explores what kidney disease is and what patients can do to slow down kidney disease through different treatment options.
Module 2: What You Need to Know About Kidney Transplants*	General Contents	Brochure	Postcards	Video
	Module 2 Card Video #2 (DVD or link)	“What you need to know about kidney transplants” o Your treatment options: Dialysis or transplant o Your treatment options: Deceased or living donor o Deceased donor kidney transplants o Kidney patient evaluation, surgery, and recovery o Possible risks of a transplant	“What are the advantages of a transplant?” “What are the 2 types of transplants?” “What is transplant evaluation like?”	“Learning more about becoming a kidney transplant recipient” This video compares the benefits and risks of dialysis, deceased donor transplant, and living donor transplant.
Module 3: What You Need to Know About Living Donation*	General Contents	Brochure	Postcards	Video
	Module 3 Card Video #3 (DVD or link)	“What you need to know about living donation“ o Kidney transplants from a living donor o Living donor evaluation, surgery, and recovery o Possible risks to a living donor	“What are the advantages of living donation?” “What is it like to donate a kidney?” “What are the risks of donating a kidney?”	“Choosing between deceased donor transplant and living donor transplant” This video explores the benefits and risks of both transplant surgeries, specifically what people should know about living donation.
Module 4: How to Decide What to Do About Your Kidney Disease*	General Contents	Brochure	Postcards	Video
	Module 4 Card Video #4 (DVD or link)	Brochure: Deciding what to do about your kidney disease o Making a decision about your treatment o Keep thinking about your treatment options o Visit websites to learn more o Choose a treatment option that’s right for you o Your next steps	“What are the pros and cons of the options?” “How can you keep learning more?” “What is the right decision for you?” “What should I do if I am interested in living donation?” “What should I consider before making a decision?”	“Deciding what to do and steps to take” This video explores patients deciding what treatment options is best for them and what steps to take.

*Excludes text message sequence as it is too large for this publication. See Table 2 for an example of the text message sequence

To expand this program for patients in CKD 3 and 4, we conducted a combination of 32 additional focus groups and individual interviews to learn what additional content should be added. Based on recommendations, we added more content about the purpose and function of kidneys, explaining in detail what kidney disease is and its various stages, how to slow down the kidney failure process, and providing an overview of treatment options once the patient enters kidney failure. Experts from the nonprofit organization, Health Literacy Media, and the study investigators reviewed and revised all print content using the most current, evidence-based health literacy principles [34]. The review and edits included considerations around audience appropriateness, readability, behavioral orientation, interactivity, information architecture, plain language, and clear design.

Each *Explore Transplant@Home* video begins and ends with a transplant educator and kidney professional or patient introducing the video and then making specific recommendations afterwards about what to think about next. The healthcare professionals on the video are diverse in their gender and ethnicity. On the final video of the series, a patient and his wife models meeting with the educator to work through the decision-aid and make a decision that is right for him or her. This modeling occurs on the video to support the patient watching and doing the same at home with his family. The Spanish language version of the video (voiced in Spanish, not subtitled) has been awarded a certificate of translation.

During the baseline survey, patients will be asked about the availability of Internet and DVD resources in their home. If the patient does not have a DVD player, a DVD player will be provided as a service of the grant. Should they prefer to watch this program via Internet streaming, an individualized login code will be provided to them. Individual login data for patients utilizing the Internet will be tracked to determine fidelity.

After each module of print and video education is mailed, postcards will be mailed weekly, recapping important content covered within the videos and brochures. Patients will have the opportunity to participate in a texting component of *ET@Home* that also sends educational content through learning reminders and questions by SMS text message each week (Table 2). Study participants will receive text messages daily that include study participation reminders, motivations to continue in the study, CKD facts, recommendations for learning more, and quiz questions to test knowledge. Participation in the text messaging portion of the trial is voluntary, and the option to opt out is available at all times.

**Table 2 Tab2:** Examples of ET@Home Text Messages

REMINDER	Your first packet “Basics of Kidney Disease” is headed your way! Keep an eye out for the postcards for this packet as well.
MOTIVATION	You can slow down how fast your kidneys fail. Learn more about all of your options!
FACT	Did you know that the kidneys help keep bones healthy?
RECOMMENDATION	Chronic kidney disease (CKD) can present itself through a variety of symptoms. It’s important that you familiarize yourself with these symptoms so you can track changes and talk to your doctor.
QUIZ QUESTION	Can you slow down how fast your kidneys fail? Reply with YES or NO.
ANSWER FOR YES	That’s right! You can slow down how fast your kidneys fail.

If patients have questions for their kidney and transplant providers, they are directed to contact the *ET@Home* Help line, which can connect them with their KPSC providers for more information.

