**Methods:**

In this RCT, 1200 English and Spanish-speaking CKD Stage 3–5 patients will be randomly assigned to one of two education conditions: *ET@Home* or KPSC standard of care education. Randomization will be stratified by CKD stage and primary language spoken. Those in the *ET@Home* condition will receive brochures, postcards, DVDs, and text messages delivering educational content in modules over a six-month period. Baseline data collection will measure demographics, transplant derailers, and the amount of previous CKD and transplant education they have received. Changes in CKD and transplant knowledge, ability to make an informed decision about transplant, and self-efficacy to pursue LDKT will be captured with surveys administered at baseline and at six months.

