## Study design

The purpose of this study is to assess whether the *ET@Home* program can be integrated successfully across a large racially, ethnically, and geographically diverse patient catchment area and to assess its effectiveness to increase knowledge about the risks and benefits of LDKT and increase informed decision-making. The effectiveness of the *ET@Home* program will be evaluated in a randomized controlled trial (RCT) of 1200 Black, Hispanic, Asian, and White patients with stage 3, 4, or 5 CKD. Patients will be randomized to receive: (1) no additional education other than what is provided within KPSC (standard-of-care); or (2) a video-guided, four-part *ET@Home* program delivered by mail and supported through bimonthly postcards and texting over six months. The study has two aims.

### Aim 1

Before intervention, to assess differences in knowledge and decision-making about the opportunities for and risks and benefits of living kidney donation for 1200 CKD Stage 3–5 patients by race/ethnicity and primary language spoken.

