### Evaluation and statistical analysis plan

#### Power analysis

Based on the following assumptions, we estimated the sample size for the RCT. Using data from previous RCTs [4, 35], a mean knowledge change score of 1.0 points is estimated necessary to be detected among patients receiving *ET@Home* and standard KPSC education. Patients’ baseline transplant knowledge scores will be correlated with those of other patients from the same clinics [intraclass correlation coefficient (ICC) of 0.31]. The variance in knowledge change has both between- and within-cluster components, yielding a pooled standard deviation estimate of 4.0. Participant retention will be 50% at the 6-month assessment. Outcomes will be assessed using two-tailed statistical tests. Type 1 error rate (alpha level) will be set at 0.05. This study design will ensure power of 0.90. Power calculations for this trial are based on all of these factors, which yields a standardized effect size, accounting for clustering of approximately 0.257.

Power analyses based on changes in transplant knowledge, our primary study outcome, are presented. The study design and analyses were treated as a test of the difference between the mean knowledge score change of CKD patients in the *ET@Home* and standard KPSC education (control) conditions six months post-baseline. It is estimated that with 600 completed surveys (50% attrition), there will be a 90% power to detect a 0.25 effect size between two equal-sized groups (control and treatment groups). By stratifying recruitment and randomization by race/ethnicity (Asian, Black, Hispanic, White), primary language spoken (English vs. Spanish), and stage of CKD, according to the table below, this sample size will also have 90% power to detect 1 point differences in change on the transplant knowledge scale between the *ET@Home* and standard KPSC education conditions for these critical subgroups using interaction terms (e.g., treatment by race interaction, language by race interaction). Patients enrolled and randomized are shown in Table 3.

**Table 3 Tab3:** Patients enrolled and randomized

Race/Ethnicity/Language	Stage of CKD			
	3^a^	4	5/ESRD	Total
*English-speaking Asian*	67	67	66	200
*English-speaking Black*	67	66	67	200
*English-speaking White*	67	67	67	200
*English-speaking Hispanic*	67	67	66	200
*Spanish-speaking Hispanic*	133	133	134	400
Total	400	400	400	1200

^a^
*CKD* 3 patient recruitment prioritized based on likelihood to progress

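### Messages to stay in the study sit inside the ET@Home texts, with no counterpart described for controls, so response to the six-month survey could differ by arm.

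*Protocol article*

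**What the plan says.** The section describing the ET@Home program presents texting as part of that program, and Table 2 is titled as examples of ET@Home messages. The Abstract (Methods) assigns the texts to the same arm: "Those in the *ET@Home* condition will receive brochures, postcards, DVDs, and text messages delivering educational content in modules over a six-month period". On content, the program section says: "Study participants will receive text messages daily that include study participation reminders, motivations to continue in the study". Facts, recommendations and quiz questions follow in the same list. It adds: "Participation in the text messaging portion of the trial is voluntary, and the option to opt out is available at all times".

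Under Study design, controls get "no additional education other than what is provided within KPSC (standard-of-care". The section on standard KPSC education says that controls who are or become potentially eligible for transplant "will not receive any additional interventions within KPSC during the study period".

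Outcome measures and research methodology takes the key outcomes from surveys at baseline and six months. Power analysis states: "Participant retention will be 50% at the 6-month assessment". This is one overall figure with no split by arm.

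Statistical analysis plans multiple imputation by chained equations using the analysis and stratification variables, analysis by assigned group, and a comparison of patients who do not complete six months. That comparison is not said to be made by arm.

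**The concern.** Encouraging people to remain in a trial is a retention task, not an educational one. Here it is bundled into the randomized treatment. If those messages change who returns the six-month survey, the two sets of completers are selected to different degrees, and the comparison between them is no longer purely the randomized one.

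With half the outcomes expected to be missing, there is ample room for such a shift. A trait such as engagement plausibly relates both to answering the survey and to gaining knowledge. Two opposite outcomes are credible. The prompts may keep less engaged ET@Home patients in, which would understate the effect. Or frequent contact may wear those patients out and leave the keen ones, which would overstate it.

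Imputation corrects the part of this selection that measured variables explain. It does not correct what remains.

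**Working it through.** **Inputs from the article.** 1200 randomized 1:1; 50% retention; SD of knowledge change 4.0; target difference 1.0 point; two-sided alpha 0.05.

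**Assumed, because the article gives no figure.** Retention by arm (55/45% and 60/40%, total held at 600 completers), and the correlation rho between response propensity and knowledge change (0.1 to 0.3, equal in both arms).

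**Step 1: the plan's own figures.** 1200 × 0.50 = 600 completers, 300 per arm, as stated. Power analysis says: "It is estimated that with 600 completed surveys (50% attrition), there will be a 90% power to detect a 0.25 effect size". With 300 per arm and no further design adjustment, I get 86.5% at 0.25 and 88.3% at 0.257, the other effect size given there. The present point does not depend on that difference.

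**Step 2: does unequal retention cost power?** Very little. At effect size 0.25 with 600 completers, power is 86.1% at 330 versus 270 and 85.1% at 360 versus 240. The issue is bias, which a larger sample would not cure.

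**Step 3: bias among completers.** Suppose a patient responds when a standard normal propensity exceeds a cut-off z that leaves a fraction p above it. The mean propensity among responders is m(p) = φ(z)/p.

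- m(0.45) = 0.880 and m(0.55) = 0.720, a difference of 0.160.
- m(0.40) = 0.966 and m(0.60) = 0.644, a difference of 0.322.

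Size of bias = SD × rho × difference in m. The standard error is 4.0 × √(1/n₁ + 1/n₂), which is 0.328 for 330 versus 270 and 0.333 for 360 versus 240. The last column is the true two-sided type I error of a completer comparison run at nominal 5%, ignoring clustering.

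| Retention | rho | Bias in points | Type I error |
|---|---|---|---|
| 55/45% | 0.1 | 4.0 × 0.1 × 0.160 = 0.06 | 5% |
| 55/45% | 0.3 | 4.0 × 0.3 × 0.160 = 0.19 | 9% |
| 60/40% | 0.1 | 4.0 × 0.1 × 0.322 = 0.13 | 7% |
| 60/40% | 0.3 | 4.0 × 0.3 × 0.322 = 0.39 | 21% |

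With positive rho, the bias runs against whichever arm retains more patients.

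**Step 4: equal completion would not settle it.** At 50% in both arms, m(0.50) = 0.798. If selection differed by arm (say rho 0.3 versus 0.1), the bias would be 4.0 × 0.2 × 0.798 = 0.64 points. This too is an assumption, shown only to mark the limit of a check on completion rates.

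**Step 5: relation to the planned analysis.** These figures are for completers before adjustment. Imputation on baseline and stratification variables would remove some of the bias, and the SD left after covariates is below 4.0, so for a given rho the figures lean high. They concern the knowledge score only; informed decision-making, the other primary outcome, was not modelled.

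**The case against.** The case against has real force.

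- **The texts shown are not survey prompts.** In Table 2 the reminder announces a mailed packet, and the motivation concerns slowing kidney disease and learning about options. The full sequence is left out for length. This stands as a limit on what can be claimed, but the body text still names study participation and continuation as content.
- **A reader might infer that controls get no survey reminders, or are barred from them.** The article does not support that. It does not describe how the six-month survey is solicited in either arm; its email and phone follow-up concerns the initial survey. Common reminders may be in the full protocol. The sentence on additional interventions covers only potentially eligible controls and is about interventions, not survey contact.
- **The phrase about study participants could be read as covering both arms.** The section, the Table 2 title and the Abstract make that reading unlikely.
- **Texting is voluntary**, which dilutes any effect on retention in the arm as a whole.
- **Contact is unequal by design.** ET@Home also brings mailed modules, postcards and a help line in an unblinded trial. Moving a few messages leaves most of that in place. True, but that contact is the intervention under test, and retention messages need not be part of it.
- **The plan already looks at non-completers and imputes.** This helps, but only for selection that measured variables explain.

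**Conclusion.** The point holds as a avoidable design weakness of uncertain size. The article places messages about remaining in the study within one arm's treatment and describes no equivalent for the other, in a trial that expects to lose half its primary outcome data.

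A reader might go further and conclude that survey return is influenced by arm, or that the treatment effect will be biased in a known direction. Nothing in the article shows either. It gives no retention by arm, and both directions are plausible. One could also assume rho 0.5 with 60/40% retention and reach 4.0 × 0.5 × 0.322 = 0.64 points, but the article supports neither value.

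Under the milder assumptions used above, the bias among completers ranges from negligible (0.06 points, 6% of the target) to material (0.39 points, 39% of the target). The case for change rests on the low cost of removing the mechanism, not on a demonstrated distortion.

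**What to change.** Separate retention contact from education.

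1. Check the full text sequence for any message about staying in the study or returning the six-month survey. Take those messages out of the ET@Home texts and send them identically to both arms, on the same dates, by a channel open to both. The secure email or phone already used for invitations would serve; controls have not been shown to have agreed to texts.
2. Keep educational and program-use messages, including packet notices, in ET@Home.
3. Within the planned analysis of non-completers, compare six-month completion and the characteristics of completers by arm. Similar rates would be reassuring but not conclusive.

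If the full protocol already solicits the survey identically in both arms, say so; only the content check and the comparison by arm then remain.

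The cost is some non-educational messages, which can be automated if sent by email, to the 600 controls, who would have slightly more study contact. The educational contrast is unchanged. Unequal contact from the education itself remains and cannot be removed this way.
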